## Abstract

**Background:**

Considerable technological advancements have recently been made with endovascular stent grafts for the treatment of abdominal aortic aneurysm (AAA). However, there is opportunity to further improve the efficiency of endovascular aneurysm repair (EVAR), which may yield better patient outcomes and lower perioperative treatment costs.

**Methods/Design:**

The Least Invasive Fast-Track EVAR (LIFE) registry was developed to determine the clinical utility and cost effectiveness of the Ovation® Prime stent graft when used under least invasive conditions using a defined fast-track protocol. The LIFE study is a prospective multicenter post-market registry of the ultra-low profile (14F) Ovation Prime stent graft when used in the treatment of patients with AAA using a fast-track protocol, consisting of appropriate patient selection, bilateral percutaneous access, avoidance of general anesthesia and intensive care unit admission, and next-day discharge. The primary endpoint of the study is the proportion of subjects that experience a major adverse event within 30 days of the initial procedure. Primary endpoint data will be compared to a target performance goal. A total of 250 subjects will be enrolled at up to 40 sites in the United States. The first subject in this study was enrolled in October 2014 and enrollment is anticipated to continue through mid-2016.

**Discussion:**

The recent development of ultra low-profile stent grafts enables EVAR using least invasive methods. A structured fast-track EVAR protocol may yield clinical and cost benefits versus standard EVAR.

**Trial registration:**

ClinicalTrials.gov Identifier: NCT02224794

## Background

Over the last decade, considerable advancements have been made with endovascular stent grafts for the treatment of abdominal aortic aneurysm (AAA). Early studies with endovascular aortic repair (EVAR) demonstrated significantly lower perioperative morbidity and mortality rates compared to open surgical resection [1]. Consequently, EVAR has rapidly become the standard of care for AAA repair at most centers. Studies with latest-generation stent grafts have focused on improving treatment durability and expanding EVAR eligibility to accommodate patients with challenging aortoiliac anatomy. Despite this recent progress, considerable opportunity exists to further improve the efficiency of EVAR, which may yield even better patient outcomes and lower perioperative treatment costs.

Typical EVAR cases involve vascular access via surgical exposure of the common femoral artery, general anesthesia, a 24-h intensive care unit (ICU) stay, and a 3-day hospitalization [2], all of which increase morbidity and significantly contribute to the total cost of EVAR. In the current economic climate, there is heightened scrutiny on health care resource utilization such that opportunities for improved surgical- and hospital-related efficiency must continue to be explored. Fast-track hospital care pathways have been adopted with increasing frequency for open aortic surgery, resulting in shorter ICU [3, 4] and hospital [5, 6] stays with reductions in morbidity [3, 4, 6] compared to traditional surgical practices. However, experience with fast-track EVAR remains limited. The common premise of fast-track EVAR includes well-selected patients with low-risk of periprocedural complications, bilateral percutaneous vascular access, and regional anesthesia with or without conscious sedation, all of which enable faster patient recovery and expedite hospital discharge. The largest study of fast-track EVAR involved 915 patients treated with bilateral percutaneous access and local anesthesia/conscious sedation [7]. Treatment success was achieved in 94 % of cases, mean hospital stay was 1.3 days, and 30-day mortality was only 0.6 %. The clinical and cost benefits associated with fast-track EVAR are potentially substantial, but currently are not well characterized. The Least Invasive Fast-Track EVAR (LIFE) registry was developed to explore the clinical utility and cost effectiveness of a defined fast-track EVAR protocol in patients undergoing elective AAA repair.

## Methods/Design

The LIFE registry is a prospective, nonrandomized, multicenter post-market study that will enroll 250 patients at up to 40 sites in the United States. The protocol for this clinical trial has been approved by the institutional review board (IRB) at each participating site. Recruitment is ongoing and additional sites, up to 40 total sites, will be added to those already named in Table 1. All patients provided informed consent before study participation. Patient enrollment began in October 2014. This study was prospectively registered at www.clinicaltrials.gov (NCT02224794).

**Table 1 Tab1:** Study Sites and Institutional Review Board

Site Name	Institutional Review Board
Central Arkansas Veterans Healthcare System	Central Arkansas Veterans Healthcare System IRB
NCH Healthcare Systems	NCH IRB
Temple University Hospital	WIRB
Wellmont Holston Valley MC	Wellmont Health System IRB
Morton Plant Hospital	BayCare Health System IRB
Swedish Heart and Vascular	WIRB
Bend Memorial Clinic	WIRB
Hartford Hospital	Hartford Health Care IRB
WVU Hospital	West Virginia University IRB
St. Luke’s Episcopal Hospital	BRANY IRB
Palomar Medical Center	WIRB
SIH Memorial Hospital	SIH IRB
Sutter Memorial Hospital	WIRB
Chandler Regional Medical Center	East Valley Regional IRB
Syracuse VA Medical Center	Syracuse VAMC IRB
Southern Ohio Medical Center	Southern Ohio Medical Center IRB
Jersey Shore University Medical Center	WIRB
St. Joseph Mercy Oakland	St. Joseph Mercy IRB
Phoenix St. Luke‘s Medical Center	WIRB
Medical University of South Carolina	MUSC IRB III
OhioHealth Research Institute	WIRB
Arizona Heart Institute	WIRB
Heart Hospital of New Mexico	WIRB
Tuscon Medical Center	WIRB
Harrison Medical Center	WIRB and Harrison Medical Center IRB
Bakersfield Heart Hospital	WIRB
Saint Jospeh Hospital	WIRB
Lutheran Medical Center	Lutheran Medical Center IRB
Middlesex Hospital	Middlesex Hospital IRB
Sacred Heart Hospital	Sacred Heart Clinical IRB
Memorial Hospital of Jacksonville (FCCI)	WIRB
Gwinnett Medical Center	WIRB
Scottsdale Healthcare-Osborn	WIRB
Northern Michigan Regional Hospital	WIRB

### Participants

Eligible patients are adults with AAA requiring elective intervention who have anatomy suitable for endovascular repair. Complete inclusion and exclusion criteria are reported in Table 2. Pre-treatment assessments will include medical and surgical history, laboratory tests for creatinine and pregnancy, spiral contrast-enhanced computed tomography, and questionnaires related to groin pain severity and health-related quality of life. Patients will be enrolled and treated with EVAR if the investigator determines that bilateral percutaneous access, avoidance of general anesthesia and ICU stay, and next-day hospital discharge are feasible based on medical history and aortoiliac anatomy. Following enrollment, patients will remain in the study regardless of whether all components of the fast-track program are completed. Patient outcomes will be recorded through hospital discharge and at the 30-day follow-up visit per the schedule of activities in Table 3.

**Table 2 Tab2:** Main study entry criteria

Main inclusion criteria
− Age ≥ 18 years
− Male or non-pregnant female
− Candidate for elective open surgical AAA repair
− AAA >5.0 cm diameter, increased ≥ 0.5 cm diameter in last 6 months, or maximum diameter > 1.5x adjacent non-aneurysmal aorta
− Suitable anatomy for endovascular repair with the Ovation Prime Stent Graft
− Suitable anatomy to allow Perclose ProGlide Suture-Mediated Closure System via the pre-close technique
Main exclusion criteria
− Dissecting or acutely ruptured AAA
− Acute vascular injury
− Prior AAA or iliac artery repair
− Mycotic AAA or active systemic infection
− Unstable angina
− Unstable peripheral artery disease with critical limb ischemia
− Congestive heart failure
− Myocardial infarction or stroke within the past 3 months
− Need for renal artery coverage (e.g. Chimney graft)
− Planned adjunctive devices (e.g. renal stent)
− Major surgery or interventional procedure within the past 30 days
− Connective tissue disease (e.g. Marfan’s or Ehler’s–Danlos syndrome)
− History of bleeding disorder or refuses blood transfusions
− Dialysis-dependent renal failure or serum creatinine >2.0 mg/dl
− Morbid obesity (BMI ≥40 kg/m^2^)
− Home oxygen use
− Patient admitted from skilled nursing facility
− Life expectancy < 1 year
− Anticipated inability to discharge patient within 1 day
− Participation in investigational device or drug clinical trial
− Intolerance/hypersensitivity to anticoagulation, contrast media, or stent graft components

**Table 3 Tab3:** Schedule of study activities

Procedure	Baseline	Procedure	Post-Procedure	1 Month
Medical/surgical history	X			
Spiral contrast-enhanced CT	X			X
Laboratory assessment (creatinine, serum pregnancy)	X			
Quality of life (EQ-5D)	X			X
Groin pain (Wong-Baker FACES Pain Rating Scale)	X		X	X
Endovascular AAA repair		X		
Adverse events		X	X	X
Assessment of ambulation and normal diet			X	

### Device

The endograft under study is ideally suited for use in a fast-track EVAR program. The Ovation Prime stent graft is characterized by a tri-modular design with the aortic body delivered via a flexible hydrophilic-coated 14 Fr OD catheter, the smallest profile of any currently commercially available stent grafts. The aortic body is comprised of a low permeability PTFE graft and a suprarenal nitinol stent with integral anchors to achieve active fixation to the aortic wall. The aortic body contains a network of inflatable channels and sealing rings that are filled during deployment with a low viscosity, radiopaque fill polymer that cures in situ to create a conformable seal to the aortic neck. The Ovation Prime iliac limbs are comprised of highly flexible nitinol stents encapsulated in low-permeability PTFE that are packaged in ultra-low profile 13-14F OD delivery system.

### Outcomes

The primary endpoint of the LIFE registry is the incidence of major adverse events through 30 days follow-up. Major adverse events are defined as any of the following events: death, myocardial infarction, stroke, renal failure, respiratory failure, paralysis, bowel ischemia, or procedural blood loss ≥ 1000 cc. All adverse events will be adjudicated by a Clinical Events Committee (CEC). Secondary endpoints of the LIFE registry include operative details, technical success, procedure- and device-related complications, patient convalescence, and ability to successfully complete all components of the fast-track protocol (Table 4). Patients will be followed in the LIFE registry for 30 days post-treatment and will undergo lifelong surveillance thereafter. A 30-day primary endpoint is appropriate since the benefits of a fast-track EVAR program are anticipated to be realized entirely in the perioperative period.

**Table 4 Tab4:** Secondary endpoints

− Serious and non-serious adverse events
− Access technical success (i.e. procedure successfully completed with bilateral percutaneous access)
− Treatment success (i.e. successful completion of least invasive protocol through discharge)
− Blood loss, including if transfusion required
− Percent of procedures completed without general anesthesia
− Anesthesia time
− Procedure time
− Contrast volume
− Fluoroscopy time
− Time to hemostasis
− Time to ambulation
− Time to normal diet
− Groin pain
− Quality of life
− Percent of subjects discharged without ICU admission
− Length of ICU stay, if required
− Length of hospital stay
− Percent of subjects discharged within only one overnight stay
− Freedom from type I & III endoleak
− Freedom from AAA rupture
− Freedom from conversion to open repair
− Freedom from AAA-related secondary interventions
− Freedom from mortality

### Hypothesis

The primary hypothesis of the LIFE registry is that the incidence of major adverse events through 30 days will be less than a target performance goal (TPG) of 10.4 %. The TPG was determined by using the 95 % upper-bound confidence interval of the 30-day major adverse event rate in the Ovation® pivotal trial (5.4 %) [8] and adding a 5 % margin.

### Statistical methods

The sample size for the LIFE registry was determined using the exact binomial method based on a one-sided 5 % significance level, an anticipated 5 % major adverse event rate, and no more than 20 % attrition. Based on these assumptions, a sample size of 250 subjects provides at least 87 % power to test the primary hypothesis. Intent-to-treat analyses will be performed, which include all patients enrolled in the registry regardless of whether the fast-track protocol is completed successfully. Subjects will be considered enrolled when the delivery catheter is inserted into the vasculature. Continuous data will be reported using mean and standard deviation or median, minimum, and maximum, depending on normality assumptions. Categorical data will be reported with counts and percentages. The incidence of major adverse events will be compared to the TPG by calculating a one-sided 95 % Wilson upper confidence interval limit. Subgroup analyses will be performed for: a) patients who complete the fast-track EVAR protocol, b) patients who undergo bilateral percutaneous access but do not complete the fast-track EVAR protocol, and c) patients who do not undergo bilateral percutaneous access.

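### The normality rule would report hospital and ICU stay without a mean, the summary most relevant to the registry's cost-effectiveness aim

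*Protocol article*

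**What the plan says.** The rule in the protocol article, Statistical methods, is: "Continuous data will be reported using mean and standard deviation or median, minimum, and maximum, depending on normality assumptions". It covers all continuous data, and no resource endpoint is exempted.

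Table 4 (Outcomes) lists "Length of hospital stay" as a secondary endpoint. It also lists ICU stay for patients who need it, the percentage leaving after a single overnight stay, and the percentage discharged without ICU admission. It lists no cost endpoint.

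The Abstract says that the registry "was developed to determine the clinical utility and cost effectiveness of the Ovation® Prime stent graft". The Background says that it "was developed to explore the clinical utility and cost effectiveness of a defined fast-track EVAR protocol".

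The Background describes usual EVAR as involving "a 24-h intensive care unit (ICU) stay, and a 3-day hospitalization". For the largest fast-track study, of 915 patients, it reports that "mean hospital stay was 1.3 days".

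Table 2 (Participants) excludes patients who are not expected to leave within one day. The text of that section keeps enrolled patients in the study even if they do not complete every fast-track component. Statistical methods also plans three subgroups, defined by completion of the fast-track protocol and by bilateral percutaneous access.

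**The concern.** A single summary per variable, chosen by distributional shape, suits a reader who wants a typical value. It does not suit resource use. Total bed-days equal the number of patients times the arithmetic mean stay, whatever the distribution, and cannot be recovered from a median, a minimum and a maximum.

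Entry is restricted to patients expected to leave the next day, and failures are retained. Stay should therefore pile up at one night with a right tail. The rule then selects the summary that omits the mean. The minimum and maximum show only the extremes, and without quartiles the size of the tail is not shown. The published result would not give average bed use, and a reader could not set it beside the cited fast-track figure, which is a mean.

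**Working it through.** **Plan's own figure.** The article gives no figure for the reporting rule. The power statement was reproduced to confirm that it is untouched. With 20% attrition, n = 250 × 0.8 = 200. Success requires at most 13 events. The exact type I error at 10.4% is 0.0391, and the power at 5% is 0.8701, which agrees with the stated 87%. At 13 of 200 events the one-sided 95% Wilson limit is 9.99%, so the cutoff holds. Nothing below enters this calculation.

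**Would the rule select the median?** The article gives no distribution of stay, so six assumed distributions in whole nights (n about 250) were tried, with 55% to 97% of patients staying one night. Each had median 1 and minimum 1. Shapiro-Wilk p was below 1e-23 in all six. The means ran from 1.04 to 2.05 nights.

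**Two assumed cohorts, n = 250, whole nights.**

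| | Case A | Case B |
|---|---|---|
| 1 night | 212 | 212 |
| 2 nights | 37 | 12 |
| 7 nights | 0 | 25 |
| 14 nights | 1 | 1 |
| Median, minimum, maximum | 1, 1, 14 | 1, 1, 14 |
| One night | 212/250 = 84.8% | 212/250 = 84.8% |

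- Case A bed-days: 212×1 + 37×2 + 1×14 = 300; mean 300/250 = 1.20.
- Case B bed-days: 212×1 + 12×2 + 25×7 + 1×14 = 425; mean 425/250 = 1.70.
- Difference: 425 − 300 = 125 bed-days, or 0.50 nights per patient.

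The whole-cohort summaries are the same in both cases.

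**How far those summaries bound the mean.** Fix 212 patients at one night and the maximum at 14. The other 38 may lie anywhere from 2 to 14 nights, with at least one at 14. The smallest total is Case A, 300 (mean 1.20). The largest is 212 + 38×14 = 744 (mean 744/250 = 2.98).

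**What the subgroups add.** Suppose the 212 one-night patients all complete the protocol and the 38 others form one subgroup. The subgroup median is the average of the 19th and 20th ordered values: 2 in Case A and 7 in Case B. The subgroups therefore separate these two cases. They still do not fix the mean. A subgroup of 38 with minimum 2, median 2 and maximum 14 needs its lowest 20 patients at 2 nights. The other 18 may lie between 2 and 14, at least one of them at 14. Subgroup bed-days then run from 37×2 + 14 = 88 to 20×2 + 18×14 = 292. The whole-cohort mean runs from (212 + 88)/250 = 1.20 to (212 + 292)/250 = 2.02.

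**ICU stay.** Mean ICU days per enrolled patient equal the proportion admitted times the mean stay among those admitted. Table 4 supplies the first factor. The rule would drop the second if ICU stay is judged non-normal.

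**The case against.** **Detail that belongs in the SAP.** Table conventions usually do, and an article need not give them. This article does state a rule, however, and the point concerns what that rule fixes, not an omission.

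**The subgroups.** A reader might infer that the two cases would look identical throughout the report. That goes too far. Next-day discharge is part of the fast-track protocol, so longer stays fall among non-completers, and the subgroup medians would partly expose the difference. They would not give the mean or total bed-days.

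**The example.** It is constructed so that the printed summaries match, and it assumes whole nights; Table 4 gives no unit for stay. If stay is recorded in hours, the median need not sit at 1. It would still not yield the mean. The bounds above do not depend on the particular values in Case B.

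**The cost aim.** A reader might infer that the cost aim becomes unattainable. The article does not support this. The rule governs reporting, and means remain computable from patient-level data, possibly in an economic analysis that is not shown.

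**The 1.3 days.** A reader might take it as the registry's benchmark. It is background on another study. The only comparator the article specifies is the 10.4% performance goal for major adverse events.

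**Scope.** Skew in procedure and recovery times is plausible, but the article offers nothing to establish it. The normality wording also names no test and leaves room for judgement. The point therefore rests on hospital and ICU stay.

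**Other Table 4 items.** The one-night percentage measures the discharge target directly, but it is 84.8% in both cases.

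**Conclusion.** The point holds in a limited form. As written, the rule would almost certainly report hospital stay, and probably ICU stay, without a mean or quartiles, although average bed use is the quantity relevant to the stated cost-effectiveness aim. In the assumed example, the same whole-cohort summaries are compatible with means of 1.20 or 1.70 nights, a gap of 125 bed-days in 250 patients.

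This rests on two assumptions: that stay is non-normal, which is inferred from the entry criteria and the retention of failures, and that stay is counted in whole nights in the illustration.

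The loss is confined to the reported summary of secondary endpoints. The data, the primary endpoint, the sample size and the power are unaffected. This is a small improvement at almost no cost, not a flaw in the registry's inference.

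**What to change.** For length of hospital stay and ICU days, report the following whatever the normality result:

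- mean (SD) with a 95% confidence interval (a bootstrap interval suits skewed data);
- median, 25th and 75th percentiles, minimum and maximum;
- for ICU days, the mean over all enrolled patients, counting 0 for those not admitted, beside the summary among those admitted.

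The mean does most of the work here. With 84.8% at one night, both quartiles equal 1 in either case above; quartiles help when fewer than three quarters leave after one night. The same dual summary can be used for the other continuous endpoints, which makes the normality switch unnecessary.

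The cost is a sentence or two in the analysis plan and slightly longer tables. It needs no new data, adds no patient burden, and leaves sample size and significance level unchanged.

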### Study progress

The first patient in this study was enrolled in October 2014 and enrollment is anticipated to continue through mid-2016. As of October 4, 2015, 149 patients have been enrolled at over 25 sites in the United States.

## Discussion

The recent development of ultra low-profile stent grafts enables EVAR using least invasive methods. However, strict patient selection criteria are crucial to improving outcomes of a fast-track EVAR program. Ideal candidates have access vessels free of heavy calcification or extreme tortuosity and have no major risk factors for prolonged procedure or hospitalization such as ruptured AAA, renal failure, and severe comorbid conditions. Bilateral percutaneous vascular access results in higher technical success, less blood loss, fewer complications, and shorter hospital stay compared to surgical cutdown [7, 9–15]. Avoidance of general anesthesia is associated with lower rates of mortality and morbidity and shorter intensive care unit and hospital stays compared to regional anesthesia [16]. Next-day hospital discharge with no ICU stay has obvious cost benefits, provided that patient safety is not compromised. The observed advantages of each separate component may potentially yield synergistic clinical and cost benefits when utilized collectively in a structured fast-track EVAR protocol. The results of the LIFE study with the Ovation Prime stent graft are anticipated to be available in late 2016.
